## Abstract

**Background:**

There is an emerging need to systematically investigate the causes for the increased cesarean section rates in Greece and undertake interventions so as to substantially reduce its rates. To this end, the ability of the participating Greek obstetricians to follow evidence-based guidelines and respond to other educational and behavioral interventions while managing labor will be explored, along with barriers and enablers. Herein discussed is the protocol of a stepped-wedge designed intervention trial in Greek maternity units with the aforementioned goals in mind, named ENGAGE (ENhancinG vAGinal dElivery in Greece).

**Methods:**

Twenty-two selected maternity units in Greece will participate in a multicenter stepped-wedge randomized prospective trial involving 20,000 to 25,000 births, with two of them entering the intervention period of the study each month (stepped randomization). The maternity care units entering the study will apply the suggested interventions for a period of 8–18 months depending on the time they enter the intervention stage of the study. There will also be an initial phase of the study lasting from 8 to 18 months including observation and recording of the routine practice (cesarean section, vaginal birth, and maternal and perinatal morbidity and mortality) in the participating units. The second phase, the intervention period, will include such interventions as the application of the HSOG (the Hellenic Society of Obstetrics and Gynecology) Guidelines on labor management, training on the correct interpretation of cardiotocography, and dealing with emergencies in vaginal deliveries, while the steering committee members will be available to discuss and implement organizational and behavioral changes, answer questions, clarify relevant issues, and provide practical instructions to the participating healthcare professionals during regular visits or video conferences. Furthermore, during the study, the results will be available for the participating units in order for them to monitor their own performance while also receiving feedback regarding their rates. Τhe final 2-month phase of the study will be devoted to completing follow-up questionnaires with data concerning maternal and neonatal morbidities that occurred after the completion of the intervention period. The total duration of the study is estimated at 28 months. The primary outcome assessed will be the cesarean section rate change and the secondary outcomes will be maternal and neonatal morbidity and mortality.

**Discussion:**

The study is expected to yield new information on the effects, advantages, possibilities, and challenges of consistent clinical engagement and implementation of behavioral, educational, and organizational interventions described in detail in the protocol on cesarean section practice in Greece. The results may lead to new insights into means of improving the quality of maternal and neonatal care, particularly since this represents a shared effort to reduce the high cesarean section rates in Greece and, moreover, points the way to their reduction in other countries.

**Trial registration:**

NCT 04504500 (ClinicalTrials.gov). The trial was prospectively registered.

Ethics Reference No: 320/23.6.2020, Bioethics and Conduct Committee, School of Medicine, National and Kapodistrian University of Athens, Athens, Greece

**Supplementary Information:**

The online version contains supplementary material available at 10.1186/s13063-024-08263-x.

## Introduction

Since 1985, the international healthcare community has considered the ideal rate for cesarean sections to be between 10 and 15% [1]. However, cesarean sections have become increasingly common in both developed and developing countries so that today, the cesarean section rate worldwide is much higher than the rate proposed by the World Health Organization (WHO) [2]. While medically required cesarean section is associated with lower maternal and neonatal mortality, it has not been demonstrated to have any benefit for mothers and offspring who do not need the procedure. Statistically speaking, data from the previous decade show that when cesarean section rates rise above 10%, there is no maternal mortality rate improvement. A cesarean section is surgery, and, as in any surgery, short- and long-term risks may be involved which can have serious after-effects for years afterwards: following the delivery, the health of the woman, her offspring child, and future pregnancies may be compromised. Such a potential is greater among women who have little to no access to full pregnancy care. For this reason, governments and clinicians have over the past few years voiced concern regarding the steep increase in cesarean section births and, thus, the possibility of long-term negative effects for both mother and child [3]. Of course, vaginal delivery, especially operative vaginal delivery can also be associated with risks and adverse events, such as failure to progress, abnormal fetal heart rate pattern, intrapartum and postpartum hemorrhage, severe perineal lacerations, pelvic floor disorders, postpartum sexual dysfunction, and fetal injuries, certain conditions require immediate conversion of vaginal delivery to an emergency cesarean section [4].

In Greece, there is a lack of accurate statistical data on the cesarean section rate, but it seems to be above 50% [5–8], with many clinicians not availing themselves of the alternatives of vaginal birth practices proven to be beneficial [9]. In 2014, HSOG (the Hellenic Society of Obstetrics and Gynecology) published a position statement expressing concerns on the high cesarean section rates in Greece. The question as to why harmful and/or unnecessary procedures are used in many cases while other beneficial practices are ignored, despite active dissemination of scientific evidence still remains largely unanswered. The fact is that the explanation for the increased cesarean section rate is not readily apparent as it is the outcome of multiple contributing factors, iatrogenic and non-iatrogenic: these include non-adherence to the international obstetric guidelines, the lack of cesarean section audits and a serious shortage of midwives [10]. Primary cesarean section can be characterized as a key factor in the overall increase of cesarean sections given the vicious cycle of recurrence of a cesarean delivery. Hence, once there has been a reduction in the factors that lead to primary cesarean section, we can expect to see a drop in cesarean section rates. It is therefore clear that each case must be individualized and carefully evaluated as to whether or not it meets the criteria based on the guidelines for cesarean delivery [11, 12].

The fact that we currently have a poor understanding of this entire situation is partly due to the absence of a standardized internationally-accepted classification system that would monitor and compare cesarean section rates in a uniform and concrete manner. To this end, the WHO has proposed the international adoption and application of the Robson classification system for the classification of cesarean sections [1]. A theoretical framework would target specific interventions to address appropriate practice patterns after delineating the barriers to the adoption of evidence-based birth practices [13, 14]. These barriers mainly include lack of knowledge or awareness, inadequate familiarity with the issue, failure to keep up with the literature, as well as such attitude issues as the inertia of previous practices, outcome expectancy, and fear of litigation for “substandard” obstetric care and “low” self-efficacy. Other external factors affecting behavior are also noted, including lack of resources, poor time management, and doubts concerning ease of process.

Key to enabling enhancement of awareness of and familiarity with best clinical practice will be rendering research information accessible and comprehensible to practitioners. The application of evidence-based guidelines on labor management is an appropriate way to deal with the mode of delivery queries so as to reduce the cesarean section rates and, thus, to substantially improve maternal and neonatal health care thereby lowering the respective morbidity rates [15–19]. Since there is no “magic formula” to change professional behavior, the best approach may be to combine several strategies focusing on the same target, such as clarifying local leaders’ opinions, convening workshops, providing educational outreach visits, including lectures and interactive case discussions, and providing charts and other reminders along with audit procedures with provision for feedback [20–26]. These additional interventions while applied during our trial are expected to contribute further and they are discussed later in the text.

We hypothesize that a multifaceted intervention that is devised to enlighten and educate birth care providers and attendants as to the efficacy of previously applied birth practices will provide them with the theoretical background and skills to interpret evidence-based birth practices and modules and to sustain them over time, which will eventually lead to reduced cesarean section rates. The study consists of two phases, namely, observational and interventional. It will assess current practice in the participating obstetric departments and the implementation of interventions. Our aim is to determine whether this set of interventions will lead to lower cesarean section rates as well as to explore any impact on maternal and neonatal morbidity. As far as we know, this will be the first randomized, controlled, prospective trial carried out to assess the effectiveness of applying specific interventions in order to implement evidence-based birth practices with the aim of reducing the unjustifiably high cesarean section rates.

## Methods

### Study design

The plan is to conduct a multicenter stepped-wedge randomized trial involving approximately 20,000–25,000 births in selected maternity care centers around Greece. The participating obstetrical units will be located in Athens and other cities throughout the country, each one reflecting its local population characteristics, whether similar or different as compared to each other. The study will include both public (National Health System (NHS) and university) and private maternity units for the purpose of assessing different types of clinical settings. An invitation for participation was sent out by the HSOG, and the units that applied with the most deliveries among the three categories (National Health System, university, and private) were included. Eligibility of each clinic to participate in the study was backed by a minimum of 5 years’ provision of obstetric services prior to intervention initiation, considering this time period necessary and sufficient for a standard operating level of the unit. In total, 22 obstetrical units will be entering the study, as shown in the study flowchart (Fig. 1, Table 1).

**Fig. 1 Fig1:**
[figure not shown]
Study flowchart

**Table 1 Tab1:** Participating units

	**Ηospital/unit**
1.	Alexandra University Hospital, Athens
2.	Papageorgiou University Hospital, Thessaloniki
3.	University Hospital, Larissa
4.	University Hospital, Ioannina
5.	Ippokratio University Hospital, Thessaloniki/3^rd^ department
6.	Ippokratio University Hospital, Thessaloniki/2^nd^ department
7.	Attikon University Hospital, Athens
8.	University Hospital, Patras
9.	Aretaieion University Hospital, Athens
10.	University Hospital, Heraklion
11.	University Hospital, Alexandroupolis
12.	NHS Hospital “Venizeleio”, Heraklion
13.	NHS Hospital “Chatzikosta”, Ioannina
14.	NHS Hospital, Agios Nikolaos
15.	NHS Hospital, Pyrgos
16.	NHS Hospital, Corinth
17.	NHS Hospital “Tzaneio”, Piraeus
18.	Iaso Private Hospital, Athens
19.	Mitera Private Hospital, Athens
20.	Diavalkanikon Private Hospital, Thessaloniki
21.	Viokliniki Private Hospital, Thessaloniki
22.	Eleftho Private Hospital, Kavala

The participating units are recruited by the trial coordinators using geographic/population criteria and the number of births per year. The births occurring in each department and the participating obstetrician will be recruited in the study given that a maximum of 11 obstetricians per department will be involved, based on the number of births allocated to each professional. If a department has more than 11 obstetricians performing deliveries, obstetricians with the larger number of births will take part. This was decided in order to clearly define the data collection of the study. The only obstetricians or pregnant women excluded from the study will be those unwilling to participate. Informed consent of the pregnant women will be obtained by the enrolled obstetricians responsible for the care of each participating woman. The consent informs the woman about the details of the trial. The number of 11 participating obstetricians per site was determined by the 11 steps of the trial (11 pairs of units involved); thus, up to 11 obstetricians were allowed to participate. This restriction to the number is standard for stepped-wedge trials and is based on the number of steps. On the other hand, the majority of participating units had approximately this number of obstetricians or fewer. In units with more obstetricians, an effort was made to include those with the higher numbers of deliveries, irrespective of their vaginal birth or cesarean section rates.

The study does not include any interventions in the mothers or their fetuses and does not involve any pharmaceutical intervention or collection and handling of biological specimens. Instead, our study intervention applies only to the obstetricians and their labor ward practice. We will determine, among others, whether a cause of the increased cesarean section rates is a lack of compliance with current guidelines on labor management or the obstetricians’ tendency to favor a date and time convenient type of surgical labor management. In either case, obstetricians’ adherence to guidelines and follow-up tools for surgical management of labor is also expected to reduce the number of unnecessary cesarean sections or misguided interventions that can lead to cesarean section and change the doctor’s approach to vaginal birth.

The stepped-wedge cluster randomized trial comprises a novel research study design composed of the sequential transition of clusters (units) from control (observation) to intervention in a randomized order, until all clusters (units) have been revealed [27–30]. In current practice, this modality is increasingly being used for the evaluation of interventions. It will also reduce all practical and financial constraints to the minimum. Furthermore, there will be an effort to ensure that all enrolled maternity care professionals working in the selected units will comply with the intervention.

Specifically, there will be a period of monitoring and recording the activities of the maternity care unit with regard to the vaginal births and the cesarean sections (routine recording). During this period, professionals will continue with their usual in-service activities. The study will begin simultaneously in all maternity units, with a minimum recording period of routine activity for 8 months. During this period, the maternal and perinatal outcomes in each unit will also be recorded in detail via completion of questionnaires. The observation and intervention period durations will vary among the units although all units will enter the study at the same time; the intervention will be initiated in a different month (step wedged) for each of them. All the units will conclude the study at the same time, 28 months later.

During the study, there will be regular discussion of the results with the participating units. Moreover, a review of the local cesarean section rates and suggestions for improvement will take place at the start of the intervention period. We will also endeavor to ensure that all maternity care professionals working in the selected units are adequately informed about the guidelines and the other proposed interventions and have understood them. A meeting will take place shortly before the initiation of the intervention period, after which there will be online communication on a regular basis (once or twice per month). Adequate information will be provided to all the staff involved in the study and the unit’s director or designee/opinion leader whose responsibility will be to inform the other team members of the study results. A member of the study’s staff will visit each unit four times per year. During the visit she/he will accommodate data acquisition and local participating obstetricians’ familiarity with the study’s platform and will also serve the study committees’ activities indicated locally. These strategies are expected to improve adherence to the intervention. There will be no blinding for the care providers (obstetricians) concerning the results of their unit.

The intervention period of the study will be 8–18 months long and the participating units will be randomized centrally by the Clinical Trials Unit of the British Columbia University of Vancouver, Canada. According to the study design, two units will enter the intervention phase each month. This will last for 11 months. The data from each birth will be inserted electronically and will be accessible to each unit in real time. No modification of the allocated interventions is accepted without an apparent need and this should be clearly reported and explained to the study’s coordinators. No obstetrical intervention individually justified for each case will be affected by the trial protocol and the study cannot cause any harm to the participating mothers and their fetuses/newborns.

More specifically, the trial phases are as follows. The first phase involves the observation and recording of cesarean sections and vaginal births and relevant information of the participating maternity hospitals (routine practice recording) and starts synchronously for all units. The second phase, which is of different duration for each maternity hospital (stepped randomization), will comprise the implementation of the interventions following their presentation and discussion by the trial coordinators and local opinion leaders with the unit’s medical and midwifery staff. During each stage of communication, it will be stated explicitly that this implementation is being monitored and evaluated. During the study, relevant questions will be answered, and requested clarification will be provided to the healthcare professionals involved. Apart from the statistics provided in the online platform, staff involved in the study will receive regular newsletters on the progress of the study and will have the opportunity to interact with the study coordinators at least one time during the onsite visit. A two-month period for collection of the last telephone questionnaires will follow after the end of the intervention period. The total duration of the study is estimated at 28 months (8 months of observation, 18 months of stepped intervention, and 2 months collecting the last telephone questionnaires), as shown in Table 2 and Fig. 2.

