**Neonatal outcomes**
Breastfeeding issues
Transient tachypnea of the newborn (TTN)
Respiratory distress syndrome (RDS)
Intracranial hemorrhage
Brachial plexus injury
Other neurologic injury
Neonatal sepsis
Neonatal jaundice
X-ray suggestive of alveolar disease
Admission in NICU
Admission for more than 48 h in NICU
Other

A separate questionnaire has been created to calculate professionals’ willingness to change: this will be completed by all participating obstetricians prior to the intervention period. The Head Obstetrician of each unit fills out another questionnaire, his perception being given special attention. Obstetric practice trends may also be affected by the perceptions and routine practice of other medical specialties in close collaboration with the obstetric unit. Thus, two different questionnaires will also be sent to the Head Anesthesiologist and the Head Neonatologist/Pediatrician of each participating hospital (unit).

The REDCap electronic data platform will be accessed by all participating professionals to insert their data. REDCap is a secure web-based application developed to capture online and offline data for clinical research and operations and to build and manage online surveys and databases. The platform is designed to provide a safe environment so that researchers may collect and store highly confidential and sensitive medical information, while access is limited to authorized persons. All participating women will be included in the data analysis.

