### Statistical analysis

All relevant baseline individual and hospital characteristics will be summarized both overall and by trial arm period. The main analysis of the primary outcome will be based on a generalized logistic regression mixed effects model, with covariates for the trial arm and a categorical term for any underlying trend. The primary effect measure will be the odds ratio for the arm estimated from this model. Depending on the data, to increase precision, the primary model may include parametric modeling of any secular trend rather than categorical.

Sensitivity analyses of the primary outcome (and primary model) may include extensions to allow for varying secular trends between clusters (random effect for time) and varying treatment effect across clusters (random interaction between cluster and trial arm). Effect modification by cluster strata (e.g., public/private) may be explored by the inclusion of a fixed effect interaction between cluster strata and arm.

Although not expected, if baseline imbalances are obvious and of clinical relevance between control and intervention periods, the above models may be adjusted for these imbalances via a further sensitivity analysis. Moreover, if any hospitals display non-adherence to the intervention guidelines, a per-protocol analysis may be conducted ensuring proper adjustment for relevant differences between those who adhere and those who do not.

Secondary outcomes of maternal and neonatal morbidity and mortality will be displayed descriptively and, where possible (sample size permitting), analyzed similarly to the primary outcome.

There will be no interim analyses as safety is not a concern. Significance of any difference in the primary outcome is set at 0.05 and at 0.01 for additional secondary outcomes. All analyses will be conducted using R statistical software.

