## Discussion

### Strengths

This is the first large-scale prospective study on cesarean sections in Greece and, simultaneously, the first stepped-wedge randomized trial on maternity care in the country. It is at the same time the first randomized trial with a full spectrum of behavioral, educational, and organizational interventions on cesarean sections internationally.

The designed study has several strengths. It will be a stepped-wedge randomized trial that is expected to enroll 20,000–25,000 births. In addition, the participating hospitals will cover the entire Greek territory and will encompass maternity units not only in large maternity hospitals in many cities but also those in smaller regional hospitals. We thus believe that the women included in the study will be highly representative of the population of Greece. Moreover, a stepped-wedge study design rather than a classic randomized controlled trial was selected in order to more precisely evaluate the different levels of implementation as well as the experience of the participating professionals simultaneously with the obtained measurements.

The primary goal is to study the effect of the implementation of interventions on the cesarean section rates in Greece; however, we will also focus on maternal and neonatal morbidity and mortality. Thus, the questionnaires will highlight the potential impact of our interventions on each unit’s outcome. An additional secondary target is to appraise the performance of Greek obstetricians with a view to improving obstetric outcomes: all positive conclusions derived from this trial will help to upgrade obstetric services in Greece in the coming years. The study is expected to yield new insights into the effects, advantages, possibilities, and challenges of the consistent implementation of guidelines and other interventions with regard to the practice of cesarean section in Greece.

Another noteworthy strength of the study is that the data will be collected not only from inpatient records (during hospitalization) but also from follow-up phone calls to the new mothers after puerperium. In this way, we expect to collect the maximum of available information and explore in depth the current and the new status of clinical practice after examining the intervention outcome. The study period is as long as required to satisfy our Steering Committee members, as an adequate study period.

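### Women enter by consent taken by the unblinded treating obstetrician and case-mix adjustment is optional, so differential enrolment between phases could appear as a fall in the cesarean rate; the stated reason for the cap of 11 obstetricians is also wrong

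*Protocol article*

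**What the plan says.** All references are to the protocol article.

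**Entry of women (Methods, Study design).** "Informed consent of the pregnant women will be obtained by the enrolled obstetricians responsible for the care of each participating woman". On exclusions: "The only obstetricians or pregnant women excluded from the study will be those unwilling to participate". The Data section adds: "All participating women will be included in the data analysis".

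**Blinding and feedback.** Study design states that obstetricians are not blinded to their unit's results and that local cesarean rates are reviewed when the intervention period starts. Table 3 lists regular e-mailed departmental reports and live departmental statistics as an intervention component. The Data section says that data collectors know when they are in the intervention, and that questionnaires are completed once the cesarean or vaginal delivery has taken place.

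**Cap on obstetricians (Study design).** "a maximum of 11 obstetricians per department will be involved, based on the number of births allocated to each professional". Where a department is larger: "If a department has more than 11 obstetricians performing deliveries, obstetricians with the larger number of births will take part". The number is tied to the 11 steps, and the reason given is: "This restriction to the number is standard for stepped-wedge trials and is based on the number of steps". The same paragraph says that most units had about 11 obstetricians or fewer, and that obstetricians were chosen regardless of their cesarean rates.

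**Analysis (Statistical analysis).** The primary model is a mixed-effects logistic regression with covariates for arm and time. On case mix: "if baseline imbalances are obvious and of clinical relevance between control and intervention periods, the above models may be adjusted for these imbalances", and this as a further sensitivity analysis. Baseline characteristics are to be summarized overall and by period.

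**Claim (Discussion, Strengths).** The authors believe that "the women included in the study will be highly representative of the population of Greece".

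**The concern.** Randomizing units to steps protects the comparison only if the births that enter are chosen in the same way before and after crossover. Here the person who obtains consent knows the phase, works in a department whose cesarean rate is being reported back, and belongs to the team that completes the form after the mode of delivery is known. If cesarean births, or women likely to have one, were enrolled less completely in the intervention phase, the recorded rate would fall without any change in practice. That is the trial's primary outcome.

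The stated primary model contains nothing that would absorb such a shift. Adjustment is left to a judgement made after looking at the data, and even then it is optional.

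A second, separate fault is the reason given for the cap. The number of steps fixes how many groups of clusters cross over. It sets no limit on how many clinicians within a cluster may take part.

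**Working it through.** **1. Inputs from the document.** Cesarean rate 57%, target reduction 8 points (to 49%, OR 0.72), ICC 0.3, significance level 0.05, 20,000 to 25,000 births, Hussey and Hughes method (all from Data). 22 units, two crossing per month over 11 months after 8 common observation months, and 26 months of births (Study design, Table 2). Two-sided testing is assumed.

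**2. The plan's own figure.** OR = (0.49/0.51)/(0.57/0.43) = 0.725, matching the stated 0.72. With equal cells, births per unit-month are 20,000/(22×26) = 35.0 or 25,000/(22×26) = 43.7. The calculation uses individual variance 0.53×0.47 and between-unit variance equal to 0.3/0.7 times that. The Hussey and Hughes standard error of the risk difference is then 0.0150 at 20,000 births and 0.0134 at 25,000. Power for 8 points is 99.96% and 99.997%, so the stated figure of more than 99% reproduces.

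**3. How small a shift becomes significant.** 1.96×0.01502 = 0.0294 and 1.96×0.01344 = 0.0263. An observed difference of about 2.6 to 2.9 points reaches p<0.05.

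**4. Effect of differential enrolment with no true effect.** Let f be the enrolment of cesarean births relative to vaginal births, in the intervention phase only. The document gives no value for f, so a range is shown. The apparent rate is 0.57f/(0.57f+0.43), and the spurious odds ratio equals f.

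| f (assumed) | Apparent rate | Spurious fall (points) | False-positive rate, 20,000 to 25,000 births |
|---|---|---|---|
| 0.95 | 0.5415/0.9715 = 55.7% | 1.3 | 13% to 16% |
| 0.90 | 0.5130/0.9430 = 54.4% | 2.6 | 41% to 49% |
| 0.85 | 0.4845/0.9145 = 53.0% | 4.0 | 76% to 85% |

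The full 8 points would need f = 0.725. About 28% of cesarean births, or 0.57×0.275 = 16% of all births, would have to go unenrolled in that phase alone.

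**5. Check by simulation.** This used 20,000 births, unequal unit sizes, a logistic model with unit and month effects, and 200 replicates per setting. False-positive rates for ICC 0.1 and 0.3 were 6% and 4.5% at f = 1, 10.5% and 10% at 0.95, 38% and 29% at 0.90, and 70.5% and 71.5% at 0.85. The estimated odds ratio was close to f throughout. Unequal unit sizes lower some of the step 4 figures but do not change the picture.

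**6. Selection through a measured factor.** Assume that 20% of enrolled women have a previous cesarean and that 90% of them deliver by cesarean. To keep the overall rate at 57%, the rate in the others must be (0.57−0.20×0.90)/0.80 = 48.75%. A fall in the enrolled share from 20% to 17% then lowers the overall rate by 0.03×(0.90−0.4875) = 1.24 points.

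**7. What the planned summaries can show.** A tabulation by period could show the shift in step 6. It could not show which births were never enrolled, nor selection on mode of delivery within a case-mix group, because both concern births that are not in the data.

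**The case against.** The strongest reply is that the document describes a risk and gives no evidence that it materialized. Only unwilling women and obstetricians are excluded, and the Data section speaks of completing a questionnaire for each birth in each hospital, so leaving out cesareans would depart from the plan's intent. This stands, and several stronger readings that a reader might infer are not supported:

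- *That no planned analysis could detect selection.* The summaries by period could show a shift in parity or previous cesarean, since the Robson groups are built into the questionnaire. The gap is limited to non-enrolment and to selection within groups.
- *That obstetricians are fed back their own rates.* The feedback described is departmental. Data are also accessible to units in real time during the study generally, so the contrast between phases is less sharp than a switch from no audit to audit.
- *That the cap biases the comparison.* It applies in both phases, binds in a minority of units, and selection ignored cesarean rates. Nothing in the text suggests that cesareans move to non-participating colleagues.
- *That bias must favor the intervention.* That direction is plausible but not established, and the timing of consent is not stated.

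It can also be said that covariates are a matter for the analysis plan. The point does not rest on an omission, however. The article itself states a data-dependent and optional trigger for adjustment. Its plan to examine confounding covers imbalance from group randomization, which is a different problem from selective entry after crossover.

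**Conclusion.** The concern holds as a recruitment-bias risk that the stated plan does little to guard against. Consent and data entry lie with unblinded staff whose department is being audited, and the only adjustment for case mix is optional and conditional on what the data show. Under the assumed enrolment ratios of 0.95 to 0.85, the apparent fall is 1.3 to 4.0 points with no change in practice. The upper end is half the target effect and exceeds the 2.6 to 2.9 points needed for significance. High power is no protection, since it makes a modest enrolment shift more likely to be declared an effect. The real ratio is unknown.

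The sentence justifying the cap is wrong as a statement about stepped-wedge designs. Its consequence is mainly for generalizability: the enrolled births are those of consenting women under at most 11 obstetricians per department, which weakens the claim that they are highly representative of the country.

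**What to change.** 1. **Adjustment.** Replace the conditional trigger with pre-specified adjustment for parity, previous cesarean and plurality, all already recorded for the Robson groups. Leave out onset of labor and presentation, because training on induction and external cephalic version may change them. The adjusted odds ratio is on a different scale from the unadjusted one, so report the unadjusted odds ratio or a standardized difference alongside it. This handles measured case mix but not selection within groups.

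2. **Check against unit totals.** Obtain monthly totals of deliveries and cesareans from each unit for the study months. Report the enrolled fraction by phase and mode of delivery, and fit the primary model to the totals as a sensitivity analysis. Interpret it cautiously where the cap binds: totals there include births of non-participating obstetricians, so the two rates can differ without selective consent and the effect is diluted.

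3. **Wording.** Delete the claim that the cap is standard for stepped-wedge trials. If enrolled and total rates diverge by phase, limit the conclusion to consenting women of participating obstetricians.

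The cost is one request for counts per unit and some analysis wording. Hospital birth figures for 2019 were already used for planning, and totals can be requested retrospectively, so this remains feasible although recruitment is close to its end.
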